## Abstract

**Background:**

Skin cancer are increasing and some types of skin cancer are among the most lethal cancers yet are easily preventable. However, sun protection interventions are rarely implemented among outdoor workers. Our prior work shows that Michigan Operating Engineers (heavy equipment operators) spend an average of 4–5 hours in the sun, about one-third reported getting sun burned at least once a summer, and over half burned more than once a summer. About three-quarters of the sample never or only sometimes used sun block.

**Methods/design:**

Using the Health Belief Model as a guide, this randomized controlled trial (RCT) will test the efficacy of four sun protection interventions targeting Operating Engineers: a) education only; b) education and mailed sunscreen; c) education and text message reminders; and, d) education, mailed sunscreen, and text message reminders. Participations in the study will be offered during regularly scheduled safety trainings at the Local 324 Training Center. Pre- and post-intervention surveys will be collected to determine changes in sunscreen use and sun burning, the primary dependent variables. The analyses will include: a) paired t-tests to determine changes over time (from pre-intervention to post–intervention) in outcome variables (sunscreen use and burning) separately in the 4 intervention groups, b) Repeated Measures Analysis of Variance (RM-ANOVA) to compare the changes in outcomes across the 4 groups, and c) t-tests on change scores as follow-ups to the RM-ANOVA to determine exactly which groups differ from each other.

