The data support the need for sun protection interventions among this Operating Engineers. Therefore, this funded Blue Cross Blue Shield of Michigan RCT will determine the efficacy of four sun protection interventions—education only, education and mailed sunscreen, education and text message reminders, and education, mailed sunscreen, and text message reminders—among Michigan Operating Engineers. The specific aim is to determine differences in changes in sunscreen use and sun burning among Operating Engineers randomized to four sun protection interventions: a) education only; b) education and mailed sunscreen; c) education and text message reminders; and d) education, mailed sunscreen, and text message reminders.

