## Methods

### Design

This study will be a randomized controlled trial testing the efficacy of four sun protection interventions (Figure 1). Pre- and post-intervention surveys will be collected to determine the primary dependent variables (changes in sunscreen use and sun burning). Institutional Review Board approval has been obtained from the University of Michiga (HUM00057711).

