#### Power analysis

Though limited research has been conducted on interventions to increase use of sunscreen among outdoor workers, a medium sized effect (as defined by Cohen) [28] is plausible based on the studies by Armstrong et al., Buller et al., and Stock et al. [29-31]. Power analysis conducted with PASS software [32] indicated a need for 256 subjects to have 80% power to detect medium sized effects on changes in sunscreen use and sunburn in tests comparing the four individual treatment groups both by tests for mean scores with alpha of .05 two tailed. This sample size will provide even more power for tests of the effects of the interventions over time (pre- versus post- intervention) separately in the four groups.

Based on our prior experience with this group, we expect to approach 460 Operating Engineers of which we expect 15% (n = 70) to be ineligible (e.g., no text messaging or cell phone) and 15% (n = 70) to refuse, allowing for 320 to be consented. Since some analyses will be conducted just on subjects with complete data, this sample size was adjusted to account for a 20% attrition rate found in our previous research on this population resulting in a final sample size of 256. This can easily be done as there are 16,000 Operating Engineers in Local 324 all of which will be eligible and our prior work has estimated that about 23% (3,680) are interested in sun protection interventions [23]. Note, however, that the main analysis will include all subjects following an intent-to-treat approach so will have a larger sample size and thus slightly higher power.

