### Procedures

#### Recruitment, randomization and Pre-intervention survey

Subjects will be recruited while they attend regularly scheduled safety training sessions provided by the Operating Engineers Local 324 Training Center. As has been done in our prior studies, the instructor or research nurse will briefly describe the opportunity to participate in research to the class. Those interested will be provided with an information pack which includes: a) an introductory information letter; b) Informed consent form; and c) the pre-intervention survey. The surveys will have random numbers on them from 1 to 4 assigning subjects to one of the four conditions. Both the study personnel and the subjects will be blinded to the condition of randomization. As requested by leadership at Michigan Local 324, all Operating Engineers, whether they enroll in the study or not, will receive the educational intervention during regularly scheduled training sessions conducted over the winter. Only those that enroll will be randomized, have their data collected, and receive the subsequent interventions during following June, July, and August.

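### Within-arm pre-post tests are called tests of intervention effects, but with education in every arm only the added effects over education can be shown

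*Protocol article*

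**What the plan says.** The Abstract (Methods/design) states the objective as follows: "this randomized controlled trial (RCT) will test the efficacy of four sun protection interventions targeting Operating Engineers: a) education only". The Background and Design sections repeat it; in the latter, "This study will be a randomized controlled trial testing the efficacy of four sun protection interventions". The Discussion presents as novel both the individual efficacy of the four interventions and their average effects.

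The Abstract lists three analyses. The first is a set of paired t-tests of pre-to-post change "in outcome variables (sunscreen use and burning) separately in the 4 intervention groups". The second is "Repeated Measures Analysis of Variance (RM-ANOVA) to compare the changes in outcomes across the 4 groups". The third is t-tests on change scores to find which groups differ. The Independent variables section adds dummy variables with education only as the reference. The specific aim in the Background is a between-arm question: "The specific aim is to determine differences in changes in sunscreen use and sun burning among Operating Engineers randomized to four sun protection interventions".

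The Power analysis section bases 256 subjects on comparisons between the treatment groups. It then adds: "This sample size will provide even more power for tests of the effects of the interventions over time". The full phrase for those tests is "tests of the effects of the interventions over time (pre- versus post- intervention) separately in the four groups".

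Under Recruitment, randomization and Pre-intervention survey, "all Operating Engineers, whether they enroll in the study or not, will receive the educational intervention". Data are collected only from those who enroll.

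**The concern.** Randomization separates the arms only by what is added to education. It therefore supports three statements: the effect of adding sunscreen, of adding text messages, and of adding both. A statement that education works, that any arm works in total, or that the four interventions work on average needs a comparison with people who did not receive education. No such people are measured.

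What remains for those statements is pre-to-post change. The baseline survey is given at training sessions, with the education delivered over the winter. The follow-up survey is mailed in the fall. Both outcome questions under Dependent variables ask about the past summer, so they refer to different summers recalled after different delays. The Follow-up section instead speaks of the prior month, which makes comparability less certain still. Weather, hours worked outdoors, recall, regression to the mean among people who volunteer for a sun protection study, and expectation after the education session can move all arms together.

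At stake is a change unrelated to the interventions being reported as their effect, most directly for education only, where no randomized contrast offers a check.

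**Working it through.** **The plan's own figure.** Inputs from the Power analysis section: 256 subjects, 80% power, medium effect as defined by Cohen, two-sided alpha 0.05. Assumed: d = 0.5 (the conventional value, not printed in the article) and equal allocation, so 256/4 = 64 per arm.

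- Two-sample t-test with n = 64 per arm: noncentrality = d·√(n/2) = 0.5·√32 = 2.83 on 126 degrees of freedom, power 0.801. The normal approximation gives 63 per arm, or 252 in total.
- Attrition of 20%: 256/0.8 = 320, which matches 460 − 70 − 70 = 320.
- An omnibus one-way ANOVA with f = 0.25 would need only about 180 subjects, and has power 0.93 at 256.

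The 256 therefore reproduces as a pairwise between-arm calculation. The trial is sized on the valid comparison.

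**What each comparison identifies.** Let S be the shift common to all arms that is not due to any intervention, E the effect of education, and A the increment of an added component.

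- Expected change, education only: S + E.
- Expected change, education plus a component: S + E + A.
- Difference between the two: A. Both S and E cancel.

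A paired t-test in the education-only arm tests S + E = 0; in another arm it tests S + E + A = 0. No contrast in the trial isolates E, and none isolates E + A. A larger sample does not help, because S is not sampling error.

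**Size under assumed shifts.** Take E = A = 0 and S of 0.1, 0.2 or 0.3 SD of the change score. The documents give no such figure, so these are assumptions. For n = 64, the paired test has noncentrality S·√64 = 8S on 63 degrees of freedom; call its rejection probability p. For one outcome, the probability that at least one of four arms rejects is 1 − (1 − p)⁴.

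| Common shift (SD of change) | Noncentrality | p per arm | At least one of four |
|---|---|---|---|
| 0 | 0 | 0.050 | 1 − 0.950⁴ = 0.19 |
| 0.1 | 0.8 | 0.124 | 1 − 0.876⁴ = 0.41 |
| 0.2 | 1.6 | 0.351 | 1 − 0.649⁴ = 0.82 |
| 0.3 | 2.4 | 0.657 | 1 − 0.343⁴ = 0.99 |

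A simulation of 20,000 trials at shifts of 0, 0.2, 0.3 and 0.5 SD agrees with the paired-test formula. In the same runs the between-arm F test on change rejected in 4.9%, 5.0%, 5.1% and 4.7% of trials. With 80 per arm (320/4, everyone consented), p for shifts of 0.1, 0.2 and 0.3 SD rises to 0.143, 0.424 and 0.755: more subjects make the paired test reject more often for the wrong reason.

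**The case against.** The best defense is that the plan does not rest on the paired tests. The Abstract gives them the purpose of describing change over time. It assigns group comparison to the RM-ANOVA and to t-tests on change scores. The specific aim is between-arm, the regression takes education only as its reference, and the sample size fits these contrasts. All of this stands.

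A reader might infer that each intervention's efficacy is to be judged by its own paired test, that arms will be ranked by which of them reach significance, or that the wider trial will choose its interventions that way. The documents support none of these. Direct between-arm tests are specified for which groups differ. The Discussion speaks of taking forward the best interventions, which is comparative language and fits those tests.

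It is also fair to say that education for everyone is a disclosed constraint, requested by the union leadership, and not an error in itself. The shift sizes are assumed and their direction is unknown: a sunnier summer could hide a benefit as easily as another could imitate one.

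These arguments do not remove the wording. The article does list education only among four interventions whose efficacy is tested, does call the within-arm tests effect tests, and does refer to average effects of all four. Because these are things it states, its brevity or a separate analysis plan is no answer.

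**Conclusion.** The point holds in a limited form. The randomized comparisons and the sample size of 256 are sound and unaffected. The article nevertheless attaches efficacy language to quantities that the design cannot identify: the effect of education, the total effect of each arm, and the average effect of the four interventions. That conclusion follows from the design and needs no assumed number.

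The size of the possible error does rest on assumptions: a shift common to all arms, 64 per arm with equal allocation, and independent arms given the shift. Within the range examined, the chance of a paired test wrongly suggesting an effect runs from about 12% to 66% per arm. The finding concerns what the trial may conclude. It does not say that the main analysis is invalid or that arms will be selected by their paired-test results.

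**What to change.** 1. Keep the Background's between-arm aim as the efficacy question, and name the between-arm contrasts as the only efficacy tests.
2. Report within-arm mean changes with confidence intervals, as description.
3. In the Power analysis section, describe the within-arm tests as tests of changes over time instead of effects of the interventions, or delete that sentence.
4. In the Abstract, Background, Design and Discussion, limit efficacy wording to the added effect of sunscreen, text messages and both over education alone, and drop the reference to average effects of the four interventions.

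The cost is wording. Sample size, procedures and the offer of education to all engineers stay as they are. The sponsor gives up claims about education alone and about average effects that the design cannot support.

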**Discussion:**

Based on the outcome of this study, we will develop a RO1 for wider scale testing and dissemination in conjunction with the International Training Center which services North America (including the US, Mexico, and Canada). Wide scale dissemination of an efficacious sun protection intervention has the potential to substantially impact skin cancer rates among this population. The ultimate goal is for high reach, high efficacy, and low cost.

**Trial registration:**

NCT01804595

## Background

The incidence of non-melanoma skin cancer is increasing [1,2] with the rates of melanoma increasing 3.1% annually since 1992 among non-Hispanic Whites [3]. While less common among Hispanics and Blacks, the rates of skin cancer are also increasing for Hispanics [4] and survival rates for Blacks are lower [5]. The risk factors predisposing a person to skin cancer include skin type, increased sun exposure, propensity to sunburns, sun burning and blistering throughout life, number of moles, and genetic susceptibility [3,6,7]. Outdoor workers are exposed to high ultra violet (UV) levels [7-9] increasing their risk of myeloid leukemia, malignant melanoma, and lip cancer [10]. Nonetheless, the rates of receiving skin examination and the use of sun protection are lower among outdoor workers compared to indoor workers [11,12], and only less than half of outdoor workers appropriately used sunscreen [13].

Previous studies have acknowledged several barriers to using sunscreen. A common belief is that those with tanned or olive skin are not at risk for skin cancer, thus protective measures need not be taken [14]. Positive attitudes towards tans are associated with decreased use of sunscreen, thus preventing outdoor workers from taking sun protection seriously [15]. Putting on sunscreen [16,17], is viewed as a hassle, and long sleeves are uncomfortable in the heat [15,18]. Men, which constitute majority of outdoor workers, may feel that it is not masculine to protect themselves from the sun [19], especially when around other males, while women feel that a tan makes them look slender and sexy [20]. In general, the perceived importance of sun protection is low among outdoor workers [21].

Operating Engineers, one group of outdoor workers, are responsible for the operation and maintenance of heavy earthmoving equipment used in the construction of buildings, bridges, roads, and other facilities [22]. Our prliminary data show that Operating Engineers are at greater risk of skin cancer since they spend an average of 4–5 hours in the sun, over 80% reported getting sunburned at least once per summer, and over half burned more than once a summer [23]. However, about three-quarters of the sample never or only sometimes used sun block and 23% showed interest in sun protection guidance [23].

The data support the need for sun protection interventions among this Operating Engineers. Therefore, this funded Blue Cross Blue Shield of Michigan RCT will determine the efficacy of four sun protection interventions—education only, education and mailed sunscreen, education and text message reminders, and education, mailed sunscreen, and text message reminders—among Michigan Operating Engineers. The specific aim is to determine differences in changes in sunscreen use and sun burning among Operating Engineers randomized to four sun protection interventions: a) education only; b) education and mailed sunscreen; c) education and text message reminders; and d) education, mailed sunscreen, and text message reminders.

### Theoretical framework

The Health Belief Model [24] was used to guide the development of the trial for Operating Engineers. The model proposes that behavior is influenced by four constructs including Perceived susceptibility (individual’s assessment of their risk of getting sunburned and subsequent skin cancer), Perceived severity (individual’s assessment of the seriousness of sun burning and subsequent skin cancer), Perceived benefits (individual’s assessment of the positive consequences of using sun protection), and Perceived barriers (individual’s assessment of the influences that facilitate or discourage adoption of sun protection behavior). The Health Belief Model also asserts that there are mediating factors including self-efficacy (confidence) [25], cues to action, socio-psychological variables, health motivation, and demographic variables. Among the four interventions, the educational component is designed to increase perceived susceptibility to and severity of sun burning and enforce the benefits of sunscreen use. Mailed sunscreen is designed to reduce barriers and will be served as a cue to action. Text messages are designed to emphasize perceived benefits and will be served as cues to action.

## Methods

### Design

This study will be a randomized controlled trial testing the efficacy of four sun protection interventions (Figure 1). Pre- and post-intervention surveys will be collected to determine the primary dependent variables (changes in sunscreen use and sun burning). Institutional Review Board approval has been obtained from the University of Michiga (HUM00057711).

**Figure 1 F1:**
[figure not shown]
Experimental design overview.

### Setting/sample/power analysis

#### Setting and sample

One of the greatest strengths of this proposal is the “buy in” that we have from leadership at the Local 324 Training Center of the International Union of Operating Engineers. While leadership has always been interested in the health of their workers, this “buy in” is even greater now that the trend in Michigan is to shift health care costs to unions [26,27]. While the educational intervention given to all Operating Engineers will be provided during winter training sessions when Operating Engineers are typically not working, the text messages and mailed sun screen summer interventions will occur during the summer when UV rays are at their highest.

Inclusion criteria are Operating Engineers who: 1) are greater than 18 years of age; 2) are interested in enrolling in the sun protection study; 3) own a cell-phone that accepts text messages; and 4) are willing to share their phone number with the study team.

#### Power analysis

Though limited research has been conducted on interventions to increase use of sunscreen among outdoor workers, a medium sized effect (as defined by Cohen) [28] is plausible based on the studies by Armstrong et al., Buller et al., and Stock et al. [29-31]. Power analysis conducted with PASS software [32] indicated a need for 256 subjects to have 80% power to detect medium sized effects on changes in sunscreen use and sunburn in tests comparing the four individual treatment groups both by tests for mean scores with alpha of .05 two tailed. This sample size will provide even more power for tests of the effects of the interventions over time (pre- versus post- intervention) separately in the four groups.

Based on our prior experience with this group, we expect to approach 460 Operating Engineers of which we expect 15% (n = 70) to be ineligible (e.g., no text messaging or cell phone) and 15% (n = 70) to refuse, allowing for 320 to be consented. Since some analyses will be conducted just on subjects with complete data, this sample size was adjusted to account for a 20% attrition rate found in our previous research on this population resulting in a final sample size of 256. This can easily be done as there are 16,000 Operating Engineers in Local 324 all of which will be eligible and our prior work has estimated that about 23% (3,680) are interested in sun protection interventions [23]. Note, however, that the main analysis will include all subjects following an intent-to-treat approach so will have a larger sample size and thus slightly higher power.

### Procedures

#### Recruitment, randomization and Pre-intervention survey

Subjects will be recruited while they attend regularly scheduled safety training sessions provided by the Operating Engineers Local 324 Training Center. As has been done in our prior studies, the instructor or research nurse will briefly describe the opportunity to participate in research to the class. Those interested will be provided with an information pack which includes: a) an introductory information letter; b) Informed consent form; and c) the pre-intervention survey. The surveys will have random numbers on them from 1 to 4 assigning subjects to one of the four conditions. Both the study personnel and the subjects will be blinded to the condition of randomization. As requested by leadership at Michigan Local 324, all Operating Engineers, whether they enroll in the study or not, will receive the educational intervention during regularly scheduled training sessions conducted over the winter. Only those that enroll will be randomized, have their data collected, and receive the subsequent interventions during following June, July, and August.

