#### Education and sunscreen

To reduce barriers to obtaining sunscreen and serve as cues to action, in addition to education, this group will be mailed sun screens three times over the summer, a supply of SPF30 sunscreen lotion (known to prevent sun burning and skin cancer) [43]. The mailing will consist of large bottles of sunscreen and a small bottle that can be refilled and attached to their huge key rings that hang off of their belts.

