#### Education and text-message reminders

Recall of sun protection messages has been shown to be problematic [44], but the provision of text-message reminders has been found to increase adherence to sunscreen application in one study [31]. Hence, in addition to education and as cues to action, this group will receive 60 unique cellular telephone text-messages in the morning on three random days per week for the months of May, June, July, August and September. Using an internet text-messaging service, the messages will be computer generated and sent to Operating Engineers and contain information about weather conditions and various reminders (e.g., “Put on sunscreen today” or “Wow, it’s a hot one, you know what to do!”). The text message bank was developed by requesting suggestions for potential text messages from students, faculty and leadership at Operating Engineers Local 324. Since positive messages have been found to emphasize the good and appeal to the listener’s desire for good, happy emotions [45], which we want to convey during the Operating Engineers working hours, negatively oriented text messages were excluded from the message bank.

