#### Additional evaluation questions

Evaluation questions (rated on a scale of strongly disagree to strongly agree) will vary depending on the intervention subjects received and will include: The educational presentation was easy to understand. The educational presentation and or mailed sunscreen and/or text message reminders were helpful. Overall I was satisfied with the presentation and or mailed sunscreen and/or text message reminders. I would recommend the sun protection intervention to others. A write in question will ask: What, if anything, would you change about the sun protection intervention?

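### The unqualified claim that subjects and staff are blinded cannot hold for subjects, and an open 1-4 arm code in the consent pack leaves allocation concealment unsecured

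*Protocol article*

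**What the plan says.** The subsection on recruitment, randomization and the pre-intervention survey contains four statements that bear on this point.

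- Contents of the pack: "Those interested will be provided with an information pack which includes: a) an introductory information letter; b) Informed consent form; and c) the pre-intervention survey".
- Allocation: "The surveys will have random numbers on them from 1 to 4 assigning subjects to one of the four conditions".
- Blinding: "Both the study personnel and the subjects will be blinded to the condition of randomization".
- Timing: "Only those that enroll will be randomized, have their data collected, and receive the subsequent interventions during following June, July, and August".

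The intervention sections describe what each arm gets beyond the education given to everyone. For the sunscreen arm, "this group will be mailed sun screens three times over the summer, a supply of SPF30 sunscreen lotion". For the text arm, "this group will receive 60 unique cellular telephone text-messages in the morning on three random days per week". The fourth arm gets both.

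The Follow-up section has the post-intervention survey mailed in the fall. The Dependent variables section measures sunscreen use and sunburn by one self-report question each. Some other survey items differ by arm: the cues-to-action item under Health belief model covariates, and the evaluation items, which "will vary depending on the intervention subjects received".

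**The concern.** There are two separate issues.

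**Blinding.** Someone who finds sunscreen in the mail or gets sun-protection texts knows what he has been given. If he then reports how often he used sunscreen and how often he burned, the outcome assessor is an unblinded subject. Over-reporting of sunscreen use by people who were sent sunscreen, or were reminded to use it, would favour the more intensive arms. A report that repeats the blinding sentence would tell readers that this threat had been controlled.

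**Allocation.** The number that fixes the arm is already on a paper handed out before consent. It is one of four values and is shared by everyone in the arm. The packs are offered in a class, and the article describes no step that hides the number. If anyone handling packs learned what one number meant, every pack with that number would be readable, and packs could be steered or exchanged. That is the usual route to selection bias.

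**Working it through.** **1. The plan's own sample size.** The Power analysis section gives 256 analysable subjects, 80% power, two-sided alpha 0.05 and a medium effect. The effect is read here as d = 0.5, Cohen's convention, since the article gives no number. A two-sample t-test needs 63.8, so 64 per arm, with power 0.801. Then 4 × 64 = 256, and 256 / (1 − 0.20) = 320 to be consented. The stated figures reproduce, and this point does not dispute them.

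**2. Can the blinding of subjects hold until the outcome is measured?**

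| Arm | Delivered after enrolment | Evident to the subject? |
|---|---|---|
| Education only | nothing further | only by inference |
| Education and sunscreen | three mailings over the summer | yes |
| Education and texts | 60 messages | yes |
| All three | mailings and messages | yes |

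Equal arms (assumed): 320 × 3/4 = 240 consented subjects, or 256 × 3/4 = 192 completers, see their treatment. The other 80 (or 64) could infer education only if the consent form describes the arms. That form is not shown, so this remains open.

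The order of events is education and enrolment at winter training sessions, then mailings and texts, then the outcome survey in the fall. Unblinding therefore comes before the outcome report in these three arms.

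**3. Personnel.** Someone has to mail sunscreen to two arms, enter phone numbers for two arms and prepare survey items that depend on the arm. Those people must know the arm. The article does not say that they also recruit subjects or handle outcome data, so blinding of those functions is possible but not described.

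**4. Timing of allocation.** The pack holds the unsigned consent form and the numbered survey together, and the number is what assigns the arm. Anyone who takes a pack and then declines has therefore already been given a number. Beside this stands "Only those that enroll will be randomized". The two can be reconciled only if the number takes effect at enrolment, and the article does not say so.

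**5. Does simple 1-4 numbering cost power?** Assume unrestricted numbering, which the article does not state. With 256 completers the smallest of the four arms averages 55.9. Setting 56 against an arm of 64 gives power 0.773 at d = 0.5, but that takes the worst arm on purpose. Averaged over the random sizes of any given pair, power is about 0.797 against 0.801 with equal arms, a loss of about 0.4 percentage points. This is negligible.

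**The case against.** The best defence is that the blinding sentence stands in the recruitment subsection and may mean only that nobody at the session knows what the number stands for. On that reading a numbered pack works like a pre-prepared envelope whose content takes effect on enrolment. Refusals would then be independent of arm, and gaps in the numbering would cause no bias under simple randomization. Everyone at the session gets the same education and arm-specific delivery comes later, so little during winter enrolment would give the code away.

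Much of this stands. A reader might infer that allocation is openly known and concealment has failed. The article does not support that, because it never says that recruiters or subjects hold the key. What it supports is that no safeguard is described and that a shared four-value code is a weak device.

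The defence does not rescue the blinding sentence, which carries no time limit and covers subjects who will later see their treatment.

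Two other stronger readings also fail:

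- A reader might infer that the outcome questions are worded differently by arm. Only the cues-to-action and evaluation items are said to vary; each outcome question is given in a single wording.
- A reader might infer a material loss of power from unequal arms. It is about 0.4 points on average, and only under an assumption about the numbering.

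It is also true that a trial of mailed sunscreen and texts cannot blind its subjects. That is a reason to correct the statement, not to keep it. Nor is this a matter of detail condensed out of an article: the mechanism, the timing and the blinding claim are all stated, and they do not fit together.

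**Conclusion.** The blinding claim is wrong as written. For subjects in three of the four arms it fails before the self-reported primary outcomes are collected: 240 of 320 consented if the arms are equal. It also cannot hold for whoever delivers the arm-specific components. This conclusion rests only on the article's description of the interventions and the survey schedule.

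On allocation, concealment is unsecured but not shown to be broken, and the sequence described sits badly with the statement that only enrolled people are randomized. This second part is a cheap improvement rather than a proven failure.

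Neither selection bias nor reporting bias can be sized from the document. The sample size is not affected.

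**What to change.** 1. Print only a unique subject ID on the survey, one that carries no information about the arm.
2. Assign the arm from a concealed list after the consent form is signed and the pre-survey completed, and before the first mailing or text. Blocking and stratification can be left to the full protocol.
3. Replace the blinding sentence with a statement of who is blinded and until when. For example: subjects and recruiters do not know the arm until summer delivery starts; delivery staff know it; the analyst works with coded arms.
4. State that both primary outcomes are self-reported by subjects who by then know what they received, and list this as a limitation.

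The cost is an allocation list and re-labelled surveys. The schedule allows it, because enrolment is at winter sessions and the text section has the first messages in May. The change does not remove reporting bias, which is inherent in these interventions. It does remove an incorrect claim and secures the allocation.
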